
### Outcome measures

Our outcomes (Table 1) will be assessed by comparing group differences, specifically group (strangulation vs control) x time interaction, as well as within-group time-course changes in outcomes.

**Table 1 pone.0344672.t001:** Outcome measures.

Outcome Measure	Type	Test/Task and Description
Blood biomarkers	Primary outcome	The primary outcome analyses will be comparing group differences (group x time interactions) and within-group time-course changes in blood biomarkers, specifically NF-L, tau, GFAP, UCH-L1, p-tau 181, p-tau 217, and S100-beta. Additional panel of inflammatory cytokines and chemokines will be explored: IL-1b,1a,2,6,8,10,17; CCL2,3,5; and VCAM, PCAM, angiopoietin, and neureglin.
Structural neuroimaging	Primary outcome	Cortical and subcortical morphometry analyses will yield macro-structural variables (thickness, volume, gyrification, sulcal depth) across the brain. For analysis of microstructural integrity, DTI and NODDI measures will be used to derive MD, axial and radial diffusivity, fractional anisotropy, NDI, ODI, and ICVF.
fMRI imaging	Primary outcome	Resting-state connectivity will be examined throughout the whole brain and specific seeded regions including the DLPFC, angular gyrus, and cingulate gyrus. Task-based fMRI using the BART will assess neural activity (inhibition and excitation) during risk-taking behaviors in the risk-reward circuitry.
Clinical assessments	Primary outcome	Cognitive function will be measured using the NIH Toolbox Cognition Battery, which examines 5 cognitive domains (executive function, episodic memory, language, working memory, and processing speed). Oculomotor function will be tested by NPC. The NPC measures will be repeated twice, and the mean NPC (in centimeters) will be used for analyses. Mental health-related symptoms will also be treated as primary outcomes, which include depression, stress, anxiety, ADHD, personality traits, and sleep.
Retinal health	Secondary outcome	Optical coherence tomography/angiography (OCT/A) will be used to assess retinal neural structure. The primary OCT variables will be macula CSF thickness (an indicator of the gain or loss of neurons or glia in the inner nuclear, ganglion cell and nerve fiber layer), and cup-to-disc ratio (an indicator of neurodegeneration at the optic disc). Retinal vascular structure will be acquired using the OCT angiography. The primary OCT/A variable examined will be FAZ area reflecting the size of the central portion of the macula which contains no blood vessels, and which increases in size with loss of capillaries in the surrounding region).
Quantitative susceptibility mapping (QSM)	Secondary outcome	Quantitative Susceptibility Mapping of whole brain, as well as regions of interest analysis, will be conducted to inspect the tissue and brain architectural response to sexual strangulation.
Semi-structured interview	Secondary outcome	The interview will assess participants’ mood, relationship status, relationship quality, sexual agency, and overall sexual behaviors. The interview will also characterize strangulation-related characteristics (e.g., onset, frequency, duration; strangulation method (e.g., both hands, ligature); and responses from being strangled (e.g., visual changes, dizziness, disorientation, loss of consciousness), which will be asked in a 5-point Likert scale (0 = none, 5 = severe), as well as their levels of enjoyment and pleasure. The study will explore various dimensions of consent, including the timing and frequency of consent, who initiates consent discussions, and whether the act has ever become uncomfortable despite initial consent.

Note: NF-L (neurofilament light), GFAP (glial fibrillary acidic protein), UCH-L1 (ubiquitin C-terminal hydrolase-L1), IL (Interleukin), CCL (C-C motif chemokine ligand), VCAM (vascular cell adhesion molecule), PCAM (Platelet endothelial cell adhesion molecule), DTI (diffusion tensor imaging), NODDI (neurite orientation dispersion and density imaging), MD (mean diffusivity), NDI (neurite density index), ODI (orientation dispersion index), ICVF (intracellular volume fraction), DLPFC (dorsolateral prefrontal cortex), BART (balloon analogue risk task), NPC (near point of convergence), ADHD (attention deficit/hyperactivity disorder), OCT/A (Optical coherence tomography/angiography), FAZ (foveal avascular zone)

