### Specific aims

Aim 1 To examine potential group differences at baseline in neurological health between the strangulation and control groups through comprehensive neurological measures.Hypotheses: (1a) Significant differences in brain activation patterns and neuronal connectivity, increases in blood biomarkers for astrogliosis, inflammation, and axonal microstructural injury, alteration in retinal integrity, and declines in cognitive, ocular-motor, and mental health function will be observed in the strangulation group compared to controls. (1b) We will explore potential mediating factors, including behavioral, history, and broader demographic factors, driving group differences in neurological health.Aim 2: To identify the acute neurological effects of sexual strangulation through the response profile of multimodal neuroimaging, blood biomarkers, cognitive and mental health assessments, and visual health assessments.Hypotheses: (2a) Within the strangulation group, significant alterations in brain activation patterns and neuronal connectivity, increases in blood biomarkers for astrogliosis, inflammation, and axonal microstructural injury, alteration in retinal integrity, and declines in cognitive, ocular-motor, and mental health function will be observed acutely (~24h) after being strangled during sex compared with baseline. (2b) The control group will have no worsening of neurological outcomes, resulting in a significant group difference at a post-acute time point. Also, individual cerebral hemodynamics via perfusion measure and fMRI activation patterns in risk and reward pathways will be explored in response to acute sexual strangulation events.Aim 3 To determine the associations between cumulative exposure to sexual strangulation and neural cellular, physiological, and functional integrities.Hypotheses: (3a) Frequent sexual strangulation will correlate with negative neurological outcomes, and this association will strengthen over time. (3b) The neurological impact of cumulative strangulation will be pronounced in blood biomarkers, indicative of astrogliosis, inflammation, and reduced axonal microstructural integrity, surface and subcortical morphology, neural activation patterns in the limbic regions, and cognitive function. (3c) Cumulative effects of sexual strangulation will also be captured through a series of mental health and visual health assessments. For those switching their sexual behavior (e.g., controls who report new onset of strangulation experiences), an exploration of how brain health changes as they initiate or cease engaging in sexual strangulation will be conducted.Aim 4: To examine longitudinal characteristics, perceptions, and experiences of sexual strangulation via semi-structured interviews.Semi-structured interviews in connection with each laboratory visit will address how one’s experiences with sexual strangulation change over time in terms of frequency, duration, methods of strangulation, consenting status, motivations, and associated symptoms. These data will not only play a crucial role in informing behavioral targets for educational guidelines and interventions, but also identify behavioral patterns and contextual factors that modify neurological outcomes. For example, our exploratory analysis will examine the role of alteration in consciousness (AIC), such as visual changes, disorientation, loss of consciousness, or dizziness) on neurological outcomes by comparing AIC and non-AIC subgroups.Exploratory Aim 5: To examine neurological implications of sexual strangulation among a pilot cohort of males.Since no neurological data related to sexual strangulation exist for males, pilot cohorts of males (n=20 per group) will be included to generate preliminary data and hypotheses for future research.Exploratory Aim 6: To explore various contextual and modulatory factors that are influencing neurological and psychological wellbeing over time in relation to sexual strangulation and non-strangulation related sex.Leveraging comprehensive assessments of participants’ demographics, prior sexual history, and contextual factors (e.g., menstrual cycle, birth control, sleep, substance/tobacco/alcohol use), we will explore how these factors contribute to individual responses to sexual strangulation and general sexual activities. This aim will include exploration of those who switch sexual behavior (e.g., stopping strangulation or control starting to engage in strangulation).

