#### Optical coherence tomography/angiography (OCT/A).

Retinal neural structure will be imaged using high-definition spectral domain OCT, which will be acquired using a Zeiss Cirrus 5000 OCT scanner. The OCT variables examined will be macula CSF thickness (an indicator of the gain or loss of neurons or glia in the inner nuclear, ganglion cell and nerve fiber layer), and cup-to-disc ratio (an indicator of neurodegeneration at the optic disc). Retinal vascular structure will be acquired using the OCT angiography (OCT/A) capability of the Cirrus 5000. The primary OCT/A variable examined will be foveal avascular zone (FAZ) area reflecting the size of the central portion of the macula which contains no blood vessels, and which increases in size with loss of capillaries in the surrounding region).

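### Macula CSF thickness, one of two primary OCT variables, is given a layer-specific neural meaning that a total thickness at the foveal centre cannot support, and no layer-specific thickness is named

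*Protocol article*

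**What the plan says.** The Retinal health row of Table 1 (Outcome measures) classes retinal health as a secondary outcome. For neural structure it states: "The primary OCT variables will be macula CSF thickness". It explains that variable as "macula CSF thickness (an indicator of the gain or loss of neurons or glia in the inner nuclear, ganglion cell and nerve fiber layer". The second primary OCT variable is "cup-to-disc ratio (an indicator of neurodegeneration at the optic disc". Vascular structure is handled separately: "The primary OCT/A variable examined will be FAZ area reflecting the size of the central portion of the macula which contains no blood vessels".

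The Methods section on OCT/A repeats the choice, "The OCT variables examined will be macula CSF thickness", with the same interpretation, and says the images are "acquired using a Zeiss Cirrus 5000 OCT scanner". Neither section names a ganglion-cell-layer or nerve-fibre-layer thickness. The note under Table 1 expands FAZ and OCT/A but not CSF.

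Under Specific aims, hypothesis 1a expects "alteration in retinal integrity, and declines in cognitive, ocular-motor, and mental health function will be observed in the strangulation group compared to controls". Hypothesis 2a makes the same prediction for the acute visit, and 3c refers more loosely to visual health.

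**The concern.** The article fixes both a variable and what a change in it means, and the two do not match. If CSF is the central subfield, the variable is a full retinal thickness over the foveal pit. The three layers named are all inner retina, which is displaced sideways from the foveal centre, so most of the thickness measured there is outer retina. A full thickness also adds all layers together and cannot attribute a change to any one of them.

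Interpretation is at stake in both directions. A null result could be reported as no change in inner retinal neurons or glia when those layers were barely measured. A difference could be reported as inner-retinal change when it reflects the outer retina or the shape of the fovea. The abbreviation adds to the problem: in a neurological protocol an unexpanded CSF can be taken for something else entirely.

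**Working it through.** The plan gives no retinal figure to reproduce. Its Sample size section draws on blood biomarkers, resting-state connectivity and cortical morphology. It states no retinal effect size, standard deviation or repeatability. The check is therefore a comparison of the stated variables with their stated meanings, followed by a conditional illustration.

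**Step 1. What each retinal variable can say about the named layers.**

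| Variable | Role in Table 1 | Bearing on inner nuclear, ganglion-cell and nerve-fibre layers |
|---|---|---|
| Macula CSF thickness | Primary OCT, neural | Total thickness; few inner layers at the foveal centre; not layer-specific |
| Cup-to-disc ratio | Primary OCT, neural | A ratio at the optic disc, not a layer thickness |
| FAZ area | Primary OCT/A, vascular | Reflects capillary loss, not neural thickness |

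No row measures the thickness of any of the three layers. The statement about foveal anatomy is general knowledge; the article does not report layer thickness by location.

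**Step 2. Conditional size.** Both inputs below are assumptions, because the documents give neither.

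- Total central-subfield thickness: about 260 micrometres.
- Share of it made up by the three layers: 10% to 25%.

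Change in the measure = total thickness × share × proportional loss in the layers. For a 5% loss:

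- Share 10%: 260 × 0.10 × 0.05 = 1.3 micrometres, and 1.3 / 260 = 0.5% of the measure.
- Share 25%: 260 × 0.25 × 0.05 = 3.25 micrometres, and 3.25 / 260 = 1.25% of the measure.

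A measure confined to the affected layers would by definition change by 5%.

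**Step 3. What this does not give.** The ratio of proportional changes is 1/share, that is 1/0.25 = 4 to 1/0.10 = 10. It only restates the assumed share. Detectability depends on the change relative to between-person spread and repeatability, and neither is available. No loss of power can be derived for the retinal outcome.

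**The case against.** Four points can be made for the plan as written.

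- *CSF thickness is not the only retinal variable.* This stands. It is one of two primary OCT variables, with FAZ area alongside for OCT/A. A reader might infer that the retinal hypotheses as a whole rest on an insensitive measure. The documents do not support that: hypotheses 1a and 2a name no layer and no direction, and cup-to-disc ratio and FAZ area also inform them. The narrower point survives, because FAZ area is classed as vascular and cup-to-disc ratio is not a layer thickness. Neither fills the neural gap.
- *The description is broader than neuron loss.* This also stands: it covers glia, gain as well as loss, and the inner nuclear layer. It does not rescue the interpretation. The inner nuclear layer is displaced from the foveal centre too, and gain is diluted in the same way as loss.
- *The insensitivity is not demonstrated.* This stands as to size. In absolute terms the contrast can be modest. A 5% loss in a layer-specific thickness of 80 micrometres (assumed) is 4 micrometres, against 1.3 to 3.25, a ratio of 4/3.25 = 1.2 to 4/1.3 = 3.1. That comparison also mixes slightly different sets of layers. It would be wrong to call CSF thickness unusable or the retinal analysis underpowered on this evidence. The mismatch between a total thickness and a layer-specific claim does not depend on these figures.
- *Retinal health is secondary.* This stands. It does not drive the sample size, and FDR control for the baseline and acute analyses is applied separately to the ocular/retinal group, so inference on biomarkers and brain imaging is untouched.

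**Conclusion.** The concern holds in a limited form. The article attaches a layer-specific neural meaning to a total thickness at the foveal centre, and names no variable that measures those layers. Neither a null nor a positive CSF result would support the stated reading. This affects the neural part of one secondary outcome and leaves the primary outcomes alone.

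The conclusion rests on two premises: that CSF means central subfield, and that inner retinal layers are sparse at the foveal centre. The 1.3-3.3 micrometre range for a 5% loss rests further on the assumed 260 micrometres and the assumed 10-25% share. It is an illustration, not an estimate of lost sensitivity. The change is worth making because it is cheap and prevents a predictable misreading.

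**What to change.** In the Retinal health row of Table 1 and in the Methods section on OCT/A:

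1. Expand CSF at first use and in the table note.
2. Describe CSF thickness as total central retinal thickness, and remove the statement that it indicates change in the three named layers.
3. Add average macular ganglion-cell-plus-inner-plexiform thickness and peripapillary nerve-fibre-layer thickness as primary OCT variables, placed in the ocular/retinal FDR family.
4. Keep CSF thickness, cup-to-disc ratio and FAZ area. Demoting them would be a preference and is not needed to cure the problem.

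The two added measures do not cover the inner nuclear layer. If that layer matters to the hypothesis, it needs its own measure or should be left out of the interpretation.

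The existing variables already imply macular and optic-disc imaging, so no new visit or device should be needed; the imaging team should confirm that the planned scans yield both thicknesses. The cost is extraction and quality control of two more variables and a larger FDR family. If NPC is counted as ocular, the named members rise from four to six. The change should be made before any retinal outcome is analysed, so that the added variables cannot look chosen on the data.

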## Methods

### Participants

This prospective cohort study will enroll a total of 240 young adults, including 200 females and a pilot cohort of 40 males. Female participants will be assigned to one of two primary groups: individuals with frequent exposure (≥4 times per month) to sexual strangulation (n = 100) and age-matched controls with no lifetime history of being strangled during sex (n = 100). An additional pilot cohort of males (n = 20 per group) will be recruited to generate preliminary data on neurological correlates of sexual strangulation in males. The recruitment is anticipated to start in late February 2026 until March 2029, and all data collection is expected to finish by May 2030. Primary analyses will finish by May 2031. Eligible participants will be between 18 and 26 years of age and recruited primarily from the Indiana University campuses and surrounding community. Longitudinal follow-up of enrolled participants will extend up to 30 months. All participants will provide electronic written informed consent prior to enrollment. The initial study protocol has been approved by the Indiana University Institutional Review Board (#27400) on Jun 04, 2025. Upon completion of primary and secondary analyses, all relevant data will be made publicly available in sites including *brainlife* and inter-university Consortium for Political and Social Research (ICPSR).

Inclusion and exclusion criteria are summarized in Table 2. For the strangulation group, inclusion requires self-report of being strangled during sex at least four times in the month prior to enrollment, which will be verified during a screening interview. Control participants must report no lifetime history of sexual strangulation. Exclusion criteria are limited to conditions necessary for participant safety or study feasibility and include head or neck injury in the past 6 months including concussions, current diagnosis of psychosis, schizophrenia, and seizure disorder, currently taking anti-psychotic medicine, history of brain aneurysm or brain tumor, and current pregnancy. Common psychiatric conditions prevalent in young adults, including depression, anxiety disorders, bipolar disorder, and attention-deficit/hyperactivity disorder (ADHD), will not be excluded and will be assessed and accounted for analytically. Additionally, participants with implanted metal/electro/magnetic devices will not undergo MRI data collection, but they will complete all other assessments; thus, not excluded from the study.

**Table 2 pone.0344672.t002:** Inclusion and exclusion criteria.

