#### Longitudinal follow-up.

All participants will enter a longitudinal follow-up phase consisting of laboratory visits every six months for up to 30 months following baseline assessment. Each follow-up visit will include repeat multimodal neurological assessments identical to baseline measures, allowing evaluation of changes in neural cellular, physiological, and functional integrity over time. Longitudinal assessments are designed to capture cumulative exposure effects and temporal trajectories of neurological health associated with sexual strangulation. Participants who change sexual behavior during the study (e.g., controls initiating sexual strangulation or strangulation participants discontinuing the behavior) will continue follow-up when feasible. Data collected prior to behavioral change will contribute to primary analyses, while post-change data will be used in exploratory analyses to examine within-individual changes.

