#### Cumulative effects.

To determine whether cumulative exposure to sexual strangulation is associated with longitudinal changes in neurological health, we will model repeated neurological outcomes collected every 6 months over 30 months using GLMMs (or linear mixed-effects models for continuous outcomes), a similar model structure to the acute aim. Each model will include a participant-specific random intercept to account for within-person correlation. Time will be modeled as a categorical variable (baseline, 6, 12, 18, 24, 30 months) for primary analyses to allow non-linear trajectories, and as a continuous variable in sensitivity analyses.

Primary longitudinal analysis will focus on: (1) overall group differences in trajectories between the strangulation and control groups via group × time interaction, and (2) within-group change over time (especially within the strangulation group) to identify when divergence from baseline emerges. Covariates will include age, prior concussion history, mental health diagnosis, and other clinically relevant time-varying factors assessed at each visit (e.g., mental health symptoms, substance use). For imaging outcomes, motion indices will be included.

To directly test the exposure-response hypotheses, we will incorporate time-varying measures of sexual strangulation exposure (e.g., frequency since last visit and cumulative frequency across follow-up; and, where available, intensity/duration and presence of alteration in consciousness) as predictors of neurological outcomes within the strangulation group. These models will estimate whether higher exposure is associated with worse neurological outcomes and whether this association strengthens over time by including exposure × time terms when appropriate.

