### Sample size

Sample size estimates were based on power calculations using pilot data and related literature. Pilot data demonstrated moderate to large effect sizes across blood biomarkers (Cohen’s d = 0.52–0.87), resting-state functional connectivity (d ≥ 1.2), and cortical morphology (d = 1.4–2.9). Using a conservative estimate of a moderate effect size (d = 0.60), an alpha level of 0.01 to account for multiple models, and a repeated-measures design, a sample of 60 females per group will provide 80% power to detect within-group acute changes and group-by-time differences. An additional pilot sample of 10 males per group will be included to generate preliminary effect-size estimates. For the cumulative longitudinal analyses, power calculations were informed by pilot data and evidence from related hypoxic and subconcussive injury models demonstrating moderate to large effects. Assuming a conservative effect size of d = 0.50, an alpha level of 0.01, and a worst-case dropout or group-switching rate of 20%, a total of 200 females (n = 100 per group) will provide greater than 80% power to detect group differences and longitudinal exposure-response effects over 30 months. To support hypothesis generation for future studies, an additional pilot cohort of 20 males per group will be included.

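### The study dates cut follow-up short for anyone enrolled after about November 2027, but the primary model and the power claim use month 30 without allowing for it

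*Protocol article*

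**What the plan says.** The Participants section gives the calendar: "The recruitment is anticipated to start in late February 2026 until March 2029, and all data collection is expected to finish by May 2030", and then "Primary analyses will finish by May 2031". The same section says: "Longitudinal follow-up of enrolled participants will extend up to 30 months". The Longitudinal follow-up section puts all participants into "laboratory visits every six months for up to 30 months following baseline assessment".

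Other parts treat 30 months as the design. The Abstract describes six-monthly follow-up over 30 months. Screening and enrollment gives priority to first- and second-year students because they are likely to remain at the university for the whole 30 months. Cumulative effects says: "Time will be modeled as a categorical variable (baseline, 6, 12, 18, 24, 30 months) for primary analyses". Sample size assumes d = 0.50, alpha 0.01 and a worst-case 20% loss to dropout or switching, and concludes that "a total of 200 females (n = 100 per group) will provide greater than 80% power to detect group differences" and exposure-response effects over 30 months.

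None of these sections mentions that follow-up length depends on entry date.

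**The concern.** Recruitment closes about 14 months before data collection ends, while the longest planned follow-up is 30 months. Late entrants will lack their later visits however well they are retained. This loss is administrative, so an allowance for dropout or switching does not cover it.

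Aim 3 depends on the later visits. Its hypothesis is that the association with exposure grows stronger over time, and the primary longitudinal analysis looks for the point at which divergence from baseline appears. Under the stated dates, the month-24 and month-30 estimates rest on the earlier entrants, and on fewer of them than the power statement implies.

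**Working it through.** **Inputs.** From Participants: recruitment from late February 2026 to March 2029, end of data collection May 2030, end of primary analyses May 2031. From Cumulative effects: visits at 0, 6, 12, 18, 24 and 30 months, with a random intercept and categorical time. From Sample size: 100 per group, d = 0.50, alpha 0.01, 20% loss. Not given, so assumed here: the accrual pattern, the within-person correlation and a two-sided test.

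**The plan's own power figure.** For a simple comparison of two means, power = Φ(d√(n/2) − 2.576). With n = 100 per group this is 83%. With n = 80 (after 20% loss) it is 72% two-sided, or 80% one-sided. The stated figure of more than 80% is thus reproduced in this simple form before loss, and only about reached after loss if the test is one-sided. The protocol does not say which contrast, sidedness or correlation lies behind it.

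**Calendar.**
- Last enrollee: March 2029 to May 2030 is about 14 months (13 to 15, depending on the days chosen), so her last visit is month 12.
- March 2029 + 30 months = September 2031, which is 16 months after data collection ends and 4 months after primary analyses are due.
- Latest entry that allows month 30: May 2030 − 30 months = November 2027, about month 21 of 37. For month 24 it is May 2028 (month 27). For month 18 it is November 2028 (month 33). For month 12 it is May 2029, after recruitment has closed.

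**Share able to reach each visit, uniform accrual (assumption), before any loss.**

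| Visit | Calculation | Can reach | Cannot reach | Per group of 100 | After 20% loss |
|---|---|---|---|---|---|
| 12 | all | 100% | 0% | 100 | 80 |
| 18 | 33/37 | 89% | 11% | 89 | 71 |
| 24 | 27/37 | 73% | 27% | 73 | 58 |
| 30 | 21/37 | 57% | 43% | 57 | 46 |

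Changing the days within the stated months moves the month-30 figure between 41.5% and 45.8%. At 43%, about 86 of 200 females are affected.

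**Month-30 share under other accrual patterns.**
- Everyone enrolled evenly within 24 months: 1 − 21/24 = 12.5%.
- Evenly within 30 months: 1 − 21/30 = 30%.
- Accrual falling linearly to zero at month 37: (1 − 21/37)² = 19%.
- Accrual rising linearly from zero: 1 − (21/37)² = 68%.

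With the planned 20% loss added, the share lacking month 30 is 1 − 0.8 × 0.875 = 30% in the first case and 1 − 0.8 × 0.81 = 35% in the falling case.

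**Planned model.** Take a random intercept with categorical time, 80 per group after loss from the start, outcome SD 1 and within-person correlation ρ. Without truncation, the variance of the group difference in change from baseline to month 30 is 2 × 2(1 − ρ)/80 = (1 − ρ)/20. With uniform truncation, 57% of each group have visits to month 30, 16% to month 24, 16% to month 18 and 11% to month 12. The information matrices of these four patterns are summed and inverted. Power = Φ(0.50/√variance − 2.576).

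| ρ | Variance, no truncation | Variance, truncated | Ratio | Power, no truncation | Power, truncated |
|---|---|---|---|---|---|
| 0.3 | 0.0350 | 0.0502 | 1.43 | 54% | 37% |
| 0.5 | 0.0250 | 0.0362 | 1.45 | 72% | 52% |
| 0.7 | 0.0150 | 0.0219 | 1.46 | 93% | 79% |
| 0.8 | 0.0100 | 0.0146 | 1.46 | 99% | 94% |

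The earlier visits of truncated participants do enter this model, but they recover little of the missing month-30 information.

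**The case against.** The strongest reply is that the protocol says up to 30 months in several places. Staggered entry with variable follow-up is a legitimate cohort design, and that wording permits it. This stands. A reader might infer that the study cannot deliver 30-month follow-up at all, and the documents do not support that: everyone enrolled by about November 2027 can reach month 30. What the wording does not do is carry variable follow-up into the recruitment priority, the primary model or the power statement.

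A reader might also take 43% as a fixed share of participants. It is the share of the recruitment window after the cutoff, and it becomes a share of participants only under uniform accrual. The main recruitment source, a campus survey, runs in the first two to three years, so front-loading is plausible.

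A further tempting reading is that the claim of more than 80% power is disproved. A two-sample test at month 30 alone gives 52% power with 57 per group and 41% with 46 (noncentral t). That is not the planned analysis, and part of its shortfall comes from the choice of test, since 80 per group without truncation already falls below 80%. Sample size does not say that its figure refers to a month-30 contrast. For a linear slope under the same truncation and loss, power is 56%, 73%, 94% and 99% at correlations of 0.3, 0.5, 0.7 and 0.8.

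Finally, truncation by entry date applies to both groups and is not driven by outcome. A likelihood-based mixed model handles it under standard assumptions. The group-by-time comparison would be biased only if the group difference varied with entry date, and nothing in the protocol suggests that it does. The loss shown here is one of precision.

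**Conclusion.** The point holds as an unreconciled conflict between the calendar and the 30-month analysis. From the stated dates alone, nobody enrolled after about November 2027 can reach month 30, and the last enrollees stop at month 12. The only loss allowed for is 20%, for dropout or switching.

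The number affected rests on an accrual pattern that the protocol does not state: about 43% if uniform, with a range of about 12.5% to 68%. Together with the planned loss, roughly 30% or more would lack month 30 even under the front-loaded patterns examined. The variance increase of 43–46% assumes uniform accrual; it would be smaller with front-loading and larger with rising accrual. Whether power stays above 80% depends on the within-person correlation and the contrast, neither of which is given. The power claim is therefore unsupported under this calendar, but not shown to be false.

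**What to change.** Reconcile the dates with the 30-month design. If the dates stay:

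- State follow-up as about 12 to 30 months, depending on entry date.
- Give the expected number per visit under a stated accrual assumption. With uniform accrual this is about 100, 100, 89, 73 and 57 per group at months 6 to 30 before loss.
- Recompute the longitudinal power with this truncation added to the 20% loss, naming the contrast, sidedness and within-person correlation.
- Report months 24 and 30 as estimates from earlier entrants, with entry date as a covariate.

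The cost is wording and one recalculation, and the stated power will probably look less favourable. If the dates are extended instead, giving the last enrollee month 30 would take data collection to about September 2031 and move the analysis date with it. Closing enrolment by November 2027, or moving the primary contrast to month 12, would also remove the conflict. Both are design choices with their own costs, and neither is required.
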